#### Analysis of Primary Outcome Measures

We intend to compare the proportion of patients with MSTS requiring blood transfusion and the amount of ABT required. The primary analysis will be based on the intention-to-treat principle. A Fisher exact test will be used to compare the 2 arms. The exact 95% CI will also be calculated for the difference in the ABT rate between the 2 arms.

#### Analysis of Secondary Outcome Measures

The progression of disease will be assessed using the internationally accepted Response Evaluation Criteria in Solid Tumors (version 1.1) [66,67]. Disease progression is defined as at least a 20% increase in the sum of the diameters of measurable target lesions (eg, lymph nodes and bone metastases with soft tissue components), unequivocal progression of nontarget lesions (eg, malignant ascites or pleural effusions), or the appearance of 1 or more new metastatic lesions.

Computed tomography of chest or abdomen and pelvis will be used to assess metastases in the lymph nodes, lung, liver, or any abdominal organ, all of which can be visualized adequately. Magnetic resonance imaging of whole spine and nuclear medicine bone will also be performed because of their increased sensitivity in detecting early new spinal or skeletal metastases [68]. A lesion identified in a follow-up study in an anatomical location that is not present at baseline is considered a new lesion and will indicate disease progression.

The OS rate will be defined as the proportion of patients who survive until the end of the study period. Median survival times and 95% CI will be estimated using Kaplan-Meier curves for experimental and control groups. The median OS times will be compared using a log-rank test. The survival rate at 6 months after surgery will also be estimated using Kaplan-Meier curves.

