**Results:**

This is the largest clinical study on use of IOCS in MSTS from various primary malignancies to date. It will provide significant clinical evidence regarding the safety and applicability of IOCS in MSTS. It will help reduce use of ABT, improving overall blood management of patients undergoing MSTS. A limitation of this study is that not all patients undergoing MSTS will survive for the follow-up period (4 years), theoretically leading to underreporting of disease progression. Study commenced in 2016 and patient recruitment continued till 2019. As of September 2019, we have collected operative data on 140 patients. However, the 2-year outcomes of about 40.0% (56/140) of patients are in the process of collection. The study is aimed to be published in the years 2023-2024.

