## Methods

### Recruitment

This study aims to recruit a minimum of 90 patients of whom 30 will receive SBT (with or with no allogeneic blood), 30 will undergo ABT, and the remaining 30 will have NBT. From our experience of treating patients with tumor, there are likely to be very few patients who receive only SBT. The majority of patients receiving SBT are likely to receive both SBT and ABT in various proportions. SBT and ABT form the 2 experimental arms, whereas patients with NBT form the control cohort. We will compare the number of patients receiving only SBT with those receiving ABT, if the sample sizes are sufficient.

Patients will be selected from specialist outpatient spine clinics or inpatient wards. These patients may be referred from an inpatient medical oncology team for management, especially in the setting of MSD with cord compression resulting in symptoms such as pain or neurology. A thorough examination of clinical history, physical examination, and review of imaging will be done, and appropriate patient management options will be discussed by the attending orthopedic surgeon. During the enrollment period, whenever a spine surgeon has obtained surgical consent for MSTS in patients with MSD, the principal investigator (NK) will be informed either by a telephone call or by text messaging.

The *research assistant* who is on-site at the National University Hospital during office hours or any member of the research team who is available will interview the patient. During this interview, the interviewer will confirm whether the inclusion criteria are fully met. The study will be explained to suitable subjects, including the advantages as well as possible intra- and postoperative risks of the reinfusion of salvaged blood. A copy of the *patient information sheet and consent form* will be provided to the patient, detailing the recruitment procedures, our objectives, hypotheses, and background information, and any queries will be addressed. Subsequently, written informed consent will be obtained from the patient.

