Blood transfusion details will be collected from anesthetists immediately after the operation. Depending on the type of blood transfusion done during the surgery, that is, ABT only or SBT with or with no ABT or NBT, the patient will be categorized into the appropriate study cohort. All patients undergoing MSTS will receive tranexamic acid as an intravenous bolus before induction of anesthesia as per the department protocol, with subsequent top-up dosages every 4 hours during MSTS. If excessive blood loss is expected during surgery, such as in a separation surgery, continuous infusion of tranexamic acid is given to the patient.

Postoperatively, all subjects will be followed up individually by their operating surgeons, as per the standard of care at the National University Hospital. No additional patient follow-up sessions by the research team will be required. Clinical data and patient outcomes will be accessed via the computerized patient support system and EPIC system at monthly intervals. All available radiological data and clinical notes from the patients’ follow-up by their treating surgeons or physicians will be reviewed by the research team. This is to determine the postoperative outcomes such as survival and disease progression. The collected data will be analyzed postoperatively at 3, 6, 12, 24, 36, and 48 months. The data collection and follow-up of available records will continue over a period of 4 years postoperatively or until the patient’s demise, whichever occurs first. The collected outcomes of the 2 experimental groups (patients who received SBT with or without ABT) will be compared with those of the control group (patients who received NBT) as well as with the available historical data from the literature.

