## Results

This study has been funded by the National Medical Research Council of Singapore in November 2016 and approved by domain-specific review board of the National Health Group in April 2016.

Data were collected from November 2016 to present (as of submission date of manuscript). Numbers recruited into study, as of submission of the manuscript, were 140. The status of data analysis and expected results are expected to be published in the years 2023-2024, when the information is available.

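### The OS rate is a crude proportion alive at an undated end of study; define it as Kaplan-Meier survival at stated times after surgery (minor)

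*Protocol article*

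**What the plan says.** The definition is in the protocol article, Analysis of Secondary Outcome Measures: "The OS rate will be defined as the proportion of patients who survive until the end of the study period". The same paragraph plans Kaplan-Meier medians with 95% CI and a log-rank test, and adds: "The survival rate at 6 months after surgery will also be estimated using Kaplan-Meier curves". The Statistical Analysis section adds crude hazard ratios and a multivariate Cox model for OS. OS is named in the Primary Objectives and in the first hypothesis, so it is a safety outcome.

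Three statements bear on what the end of the study period can mean:

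- Entry was staggered (Abstract, Results): "Study commenced in 2016 and patient recruitment continued till 2019". The Results section puts the start of data collection in November 2016.
- Follow-up is planned per patient (Recruitment): "The data collection and follow-up of available records will continue over a period of 4 years postoperatively or until the patient’s demise, whichever occurs first".
- Follow-up is passive (Recruitment): "No additional patient follow-up sessions by the research team will be required". Outcomes are read from hospital records.

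As of September 2019 the Abstract reports that "the 2-year outcomes of about 40.0% (56/140) of patients are in the process of collection".

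**The concern.** A survival rate needs a time point and a way to treat patients whose status at that time is unknown. The definition gives neither, and its end point can be read in two ways.

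- **Calendar end.** A patient operated on in 2016 must survive almost three years longer than one operated on in late 2019 to be counted as a survivor. The proportion then averages survival over many follow-up lengths.
- **48 months per patient.** The time point is now fixed, but a patient whose records stop early has no defined place in the numerator or the denominator.

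A reader of the final report will take an OS rate as survival to some stated time and may set it beside published figures; the Recruitment section plans comparison with historical data from the literature. The number should therefore have a clear meaning.

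**Working it through.** **Plan's own figure.** 56/140 = 0.400, which matches the stated 40.0%. The article gives no expected OS rate, median or event count, so the survival inputs below are assumptions.

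**Inputs.** Entry is taken as uniform over 34 months (November 2016 to September 2019, from the Abstract and Results). Survival is assumed exponential with median m, the same for everyone, so λ = ln 2 / m and S(t) = 2^(−t/m).

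**Reading 1: calendar end at month T after first entry.** For patients entering between months a and b, the expected proportion alive is

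[exp(−λ(T−b)) − exp(−λ(T−a))] / [λ(b−a)].

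Example with m = 10, T = 46 (12 months after last entry), all entrants: (0.4353 − 0.0412) / (0.0693 × 34) = 0.167. True S(24) is 0.189 and S(48) is 0.036, so the crude value matches neither.

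The result depends strongly on T, which the article does not give. The table shows the proportion alive under one identical survival curve:

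| Median (months) | Calendar end | All | First-half entrants | Second-half entrants | True S(48) |
|---|---|---|---|---|---|
| 10 | 12 months after last entry | 16.7% | 7.9% | 25.6% | 3.6% |
| 10 | 48 months after last entry | 1.4% | 0.6% | 2.1% | 3.6% |
| 18 | 12 months after last entry | 35.1% | 24.0% | 46.2% | 15.7% |
| 18 | 48 months after last entry | 8.8% | 6.0% | 11.6% | 15.7% |

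The half-and-half split is an illustrative extreme. With a milder pattern, in which one group's entry rate falls linearly and the other's rises, m = 10 gives 10.7% vs 22.8% at 12 months after last entry but 0.9% vs 1.9% at 48 months after. At m = 18 the figures are 27.7% vs 42.6% and 6.9% vs 10.6%.

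Kaplan-Meier at a fixed time does not have this problem. In 2,000 simulated studies with 30 per group, m = 12 and T = 34, mean 6-month Kaplan-Meier survival was 0.708 for first-half and 0.707 for second-half entrants, against a true 0.707.

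**Reading 2: 48 months per patient.** With complete vital status the proportion alive estimates S(48), whatever the entry dates. Now let d be the probability of being lost by 48 months in the absence of death, at constant rate μ = −ln(1−d)/48. For m = 18 and d = 20%:

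- λ = 0.0385, μ = 0.00465, S(48) = 2^(−48/18) = 0.157.
- Observed alive at 48 months: 0.1575 × 0.80 = 0.126.
- Lost before 48 months and before death: μ/(λ+μ) × (1 − 0.126) = 0.1077 × 0.874 = 0.094.
- Lost counted as alive: 0.126 + 0.094 = 0.220.
- Lost counted as dead: 0.126.
- Lost dropped: 0.126 / (1 − 0.094) = 0.139.

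| Median, loss d | True S(48) | Lost as alive | Lost as dead | Lost dropped |
|---|---|---|---|---|
| 12, 20% | 6.25% | 12.1% | 5.0% | 5.4% |
| 18, 10% | 15.7% | 18.8% | 14.2% | 14.9% |
| 18, 20% | 15.7% | 22.0% | 12.6% | 13.9% |
| 18, 30% | 15.7% | 25.4% | 11.0% | 12.9% |
| 24, 20% | 25.0% | 31.1% | 20.0% | 22.5% |

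**The case against.** The strongest reply is that the study period means each patient's 4-year window. The Recruitment, Limitations and Abstract sections all describe follow-up as 4 years. Publication is expected in 2023-2024, and a patient operated on in September 2019 reaches 48 months in September 2023. On that reading staggered entry does not matter, and with complete vital status the proportion is a valid estimate of 48-month survival. This stands, so one cannot say that the quantity estimates no survival probability under any reading. What remains is that the definition is not tied to 48 months, and that passive follow-up does not assure complete status.

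A second reply is that group comparisons of OS use log-rank, Kaplan-Meier and Cox methods. This also stands, and no test of the crude rate between groups is specified. A reader might infer that salvaged blood could look falsely safe or falsely harmful because salvage use changed over 2016 to 2019. The documents do not support that: the nonrandomized design leaves it possible, but nothing says that entry dates differ by group. The large early-versus-late contrasts also need a calendar end soon after the last entry, which the article does not plan.

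A reader might likewise take 56/140 as 40% missing data. It is a progress count in September 2019 for outcomes still being collected, and says nothing about completeness at the final analysis.

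Finally, an article may leave censoring detail to a fuller document, and the text does not expressly rule out a Kaplan-Meier calculation of the rate. But the article does not merely omit a detail. It states a definition, as a proportion, while naming Kaplan-Meier for the median and 6-month survival next to it.

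**Conclusion.** The point holds in limited form and is minor. As worded, the OS rate either mixes follow-up lengths (calendar end) or depends on an unstated treatment of lost patients (48 months per patient). In the second case the distortion at an assumed median of 18 months and 20% loss runs from about 3 percentage points too low to 6 too high around a true 15.7%; it vanishes if vital status is complete. In the first case its size depends on the calendar end. At 48 months after last entry, the linear-drift contrast between groups with identical survival is 1 point at a median of 10 months and about 4 points at 18 months. These figures rest on exponential survival, uniform or linearly drifting entry, and assumed medians and loss rates, none of which the article gives. The effect is confined to the reported OS rate; the planned inferential comparisons of OS are not affected.

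**What to change.** Replace the definition with one sentence: OS rates are Kaplan-Meier survival probabilities at stated times after surgery (for example 6, 12, 24 and 48 months), with 95% CI, censoring each patient without a recorded death at the date last known alive. Drop the crude proportion as an outcome.

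The cost is one sentence. The Kaplan-Meier curves are already planned and the proposed times are among the planned analysis times. No new data are needed beyond the date each patient was last known alive, which the planned survival analyses already require.

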### Ethical Considerations

The domain-specific review board of the National Healthcare Group, Singapore (reference numbers: 2014/00065 and 2022/00866), has granted ethical approval for this study. Written informed consent regarding participation in this research study and receiving SBT will be obtained from each patient before the patient is recruited for the study. Data have been anonymized and deidentified. No compensation was provided to patients for this study.

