**Objective:**

This study aims to analyze safety of IOCS-leukocyte depletion filter (LDF)–processed blood transfusion for patients undergoing MSTS by assessing clinical outcomes—disease progression: tumor progression and overall survival. This study evaluates whether reinfusion of IOCS-LDF–processed blood reduces ABT rates in patients undergoing MSTS by sorting patients undergoing MSTS who require ABT into patients who consent to receive or not receive SBT.

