### Statistical Analysis

We have defined *disease progression* as the increase in the size of an existing metastatic lesion or the appearance of a new lesion in the lung, liver, or the spinal column, which can be visualized by using radiological imaging.

Demographic and clinical characteristics of patients will be summarized using mean (SD) values for continuous variables with approximately normal distribution, median (IQR) values for continuous variables with skewed distribution, and frequency (percentage) for categorical variables. A 1-way ANOVA will be used to compare the mean of a normally distributed variable across the 3 blood transfusion groups, whereas a Kruskal-Wallis rank test will be used for the comparison of medians. A Fisher exact test will be implemented for categorical variables accounting for potential small frequencies.

The association between individual characteristics and OS will be studied by using the Kaplan-Meier curve and a log-rank test. The crude hazard ratio and its 95% CI will be used to measure the association between individual characteristics and OS and will be calculated based on their original definitions. Multivariate Cox proportional hazard regression will then be used to adjust for statistically significant confounders for the relationship between the type of blood transfusion and OS. The proportional hazards assumption will be tested after the final model is obtained.

The association between the type of blood transfusion and tumor progression will be investigated by the competing risks analysis, taking death without tumor progression as the competing event. First, cumulative incidence curves of the 3 blood transfusion groups will be plotted nonparametrically, and then we will model the relation via a subdistribution hazard regression model. The measure of association will be quantified by the crude subdistribution hazard ratio; its 95% CI and *P* value will be analyzed in a univariate analysis. Subsequently, a multivariate analysis will be used to adjust for potential confounders. All statistical analyses will be done using Stata Special Edition 14.0 (StataCorp LP). The statistical tests will be assumed to be 2-sided, with the conventional 5% significance level.

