### Broader Implications

Through the reporting of our analysis, this study will help reduce the use of ABT, reduce the burden on blood banks, and improve the overall blood management of patients with MSTS. This improvement in blood management will prevail even with the improvement of surgical techniques in the management of MSTS, that is, introduction of minimally invasive surgery techniques and the regular use of navigation. This is because the 2 techniques mentioned earlier will reduce blood loss during the steps of spinal instrumentation but are unlikely to have any effect on blood loss while performing decompression. Decompression and separation surgery presently still form a major component of MSTS and will continue to do so, resulting in significant bleeding that requires replenishment potentially in the form of SBT.

In this protocol, we have proposed a prospective observational nonrandomized study design as the ethical appropriateness of blinding or randomizing these patients is a key concern in our region and country. Blinding or randomization of patients with MSD could be deemed unethical, especially among patients who may not agree to receive SBT or ABT as this will limit the blood transfusion type applicable for them. This could be attributed to the current lack of clinical evidence that SBT does not lead to disease progression or shortened survival among patients undergoing MSTS who receive SBT. With this research proposal, we aim to highlight the safety profile of SBT, together with a design protocol applicable for use in patients with MSD. Future research, such as propensity-matched studies, can be done to further validate the outcomes from our current protocol.

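### The ABT-reduction comparison has incompatible rules for forming its groups: consent to SBT, consent required from everyone, and blood actually given

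*Protocol article*

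**What the plan says.** Five places in the protocol article bear on who is compared with whom.

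- **Abstract, Objective.** The ABT-reduction question is to be answered by "sorting patients undergoing MSTS who require ABT into patients who consent to receive or not receive SBT".
- **Ethical Considerations.** "Written informed consent regarding participation in this research study and receiving SBT will be obtained from each patient before the patient is recruited".
- **Recruitment, consent.** After the study and the risks of reinfusion are explained, "Subsequently, written informed consent will be obtained from the patient". Agreement to SBT is not named here as a condition.
- **Recruitment, cohorts.** Patients are placed in a cohort after the operation: "Depending on the type of blood transfusion done during the surgery", they are ABT only, SBT with or without ABT, or NBT. The planned minimum is 30 with SBT, and "30 will undergo ABT, and the remaining 30 will have NBT".
- **Analysis of Primary Outcome Measures.** The ABT rate is compared between two arms with a Fisher exact test and an exact 95% CI, and "The primary analysis will be based on the intention-to-treat principle".

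The ABT-rate question stands under Secondary Objectives, although its analysis is headed as primary.

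**The concern.** An intention-to-treat comparison needs groups fixed before the event being counted, here before blood is given. The Objective offers such a split (consent to SBT, yes or no). The ethics statement, taken at its word, removes one half of it. The Recruitment rule ignores consent and forms the groups from the transfusion itself, which is also the outcome.

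At stake is whether the ABT-reduction question can be answered with the patients enrolled, and what the ABT-only cohort represents. If decliners were admitted, that cohort may include patients selected by their own choice before surgery. If they were not, it consists only of patients who agreed to SBT and then received none, who are selected by what happened in theatre. Those two groups do not overlap and raise different confounding questions, including for tumor progression and overall survival.

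**Working it through.** The article states no figure for this point, and the minimum of 90 is only 30 + 30 + 30. The check is therefore a comparison of the rules, plus the arithmetic that the cohort definition forces.

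**Step 1: each rule alone.**

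| Rule | Groups formed by | When fixed | SBT decliners in the study |
|---|---|---|---|
| Abstract, Objective | consent to SBT, yes/no | before surgery | needed as comparators |
| Ethical Considerations, plain words | (entry condition) | before recruitment | 0 |
| Recruitment | blood actually given | after surgery | not considered |
| Analysis of Primary Outcome Measures | two arms, intention to treat | must be before surgery | not stated |

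The first two rows contradict each other. The third cannot supply what the fourth needs.

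**Step 2: the ABT rate under the Recruitment rule.** Take the planned minimum of 30 per cohort and count ABT during surgery. Let x be the number in the SBT cohort who also received ABT.

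- ABT cohort: 30/30 = 100%, by definition.
- NBT cohort: 0/30 = 0%, by definition.
- SBT cohort: x/30, the only free quantity.
- SBT minus ABT: x/30 − 30/30 = −(30 − x)/30, which can never be positive.
- SBT minus NBT: x/30 − 0 = x/30, which can never be negative.

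The direction of each difference is fixed before any data are seen.

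**Step 3: what the Fisher test would then do.** Suppose k = 30 − x patients in the SBT cohort received salvaged blood only. Against 30/30, the two-sided Fisher P value is 2 × C(30,k)/C(60,k).

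- k = 5: 2 × 142,506/5,461,512 = 0.052
- k = 6: 2 × 593,775/50,063,860 = 0.024

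At the stated level ("2-sided, with the conventional 5% significance level"), six SBT-only patients among 30 would give a significant reduction in ABT, whatever salvage does. The test would merely count SBT-only patients. The values of k are illustrative. Recruitment expects very few such patients but gives no number.

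**Step 4: the alternative.** Grouping by SBT consent recorded before surgery leaves the ABT rate free to vary on both sides. No other two-group split fixed before surgery appears in the article. Under the plain words of Ethical Considerations, the decliner side has 0 patients.

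**The case against.** **The ethics wording may be loose.** It is an ethics statement, not an eligibility list, and it could mean that each patient's decision on SBT is documented either way. Recruitment does not make agreement to SBT a condition, and the full inclusion criteria and consent form are not shown. This is a fair reading, but the sentence says that consent is obtained from each patient, and nothing in the article gives the looser sense. If that was the intent, a sentence saying so is still needed.

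**The consent split appears once, in the Abstract.** The secondary objectives, the hypotheses and the methods do not repeat it, so it may be a stray phrase. This also stands in part. Removing the phrase, however, leaves the intention-to-treat analysis with no groups fixed before surgery.

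**Stronger readings that the article does not support:**

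- A reader might infer that the Objective makes all 30 patients of the ABT arm decliners. It does not. Recruitment defines that cohort by blood given, so it could mix decliners with consenters who were not reinfused.
- A reader might take ABT-only patients as the main comparator. The article names NBT as the control cohort.
- A reader might cite Broader Implications, which argues against randomization "especially among patients who may not agree to receive SBT or ABT as this will limit the blood transfusion type applicable for them", as proof that decliners were enrolled. It foresees refusals but does not say that those patients enter the study.
- A reader might supply reasons why a consenter was not reinfused. The article gives none.

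Selection by intraoperative events follows from assigning cohorts by blood given, and would remain even if the ethics sentence were reworded.

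**Conclusion.** The inconsistency is real and reaches the analysis headed as primary. The Objective, the ethics statement, the cohort rule and the intention-to-treat statement cannot all be followed. With cohorts formed by blood given, the ABT rate is 100% in one cohort and 0% in another by construction. With groups formed by consent, the analysis has meaning, but the ethics wording read strictly leaves no decliners to compare.

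This rests on two assumptions. First, the ethics sentence is taken at its plain meaning. Second, the ABT rate is counted over the operation, the same window that defines the cohorts. If postoperative transfusions were also counted, the NBT rate could rise above 0%, but the ABT cohort would stay at 100%. How many of the 140 recruited patients declined SBT cannot be told from the article.

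**What to change.** Before analysis:

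1. State whether patients who declined SBT were eligible, and bring the Abstract's Objective, Ethical Considerations, Recruitment and Analysis of Primary Outcome Measures into line.
2. For the 140 enrolled patients, take preoperative SBT consent status from the signed forms and hold it as a baseline variable.
3. Make the ABT-rate intention-to-treat comparison by that status, with all enrolled patients in the denominator rather than only those who turned out to need ABT. It remains a nonrandomized comparison and should be described as one.
4. Report the ABT-only cohort split into decliners and consenters who received no salvaged blood.
5. If every enrolled patient consented to SBT, withdraw the consent-based objective and the intention-to-treat label, and describe the ABT-only cohort as consenters who received no salvaged blood.

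The cost is a few sentences of text and one variable from existing forms, provided the forms record the SBT decision. Rewording entry consent would no longer help, since the Abstract reports that recruitment ran until 2019. The real downside is that the consent-based comparison may have to be dropped if few or no decliners were enrolled.
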